##### Fatigue

The Functional Assessment of Chronic Illness Therapy-Fatigue (FACIT-F) measure will be used to assess cancer-related fatigue. FACIT-F is a 13-item scale that asks respondents to rate statements regarding their fatigue experiences and its impact on their daily lives. Sample items include the following: ‘I feel fatigued’, ‘I feel weak all over’ and ‘I feel listless’. Items are measured on a 4-point Likert scale from 0 (not at all) to 4 (very much). Items are summed to provide an overall score ranging between 0 (severe fatigue) and 52 (no fatigue) [91]. This item was designed specifically for use with cancer patients [92].

##### Self-efficacy for coping with cancer

The Cancer Behaviour Inventory-Brief version (CBI-B) is a 12-item measure of self-efficacy expectations about coping with cancer [93]. Participants report their level of confidence for the items on a Likert scale from 1 (not at all confident) to 9 (totally confident). Items are summed to provide a general estimate of coping efficacy, with higher scores indicating a higher degree of self-efficacy in coping with cancer. This measure has been found to be a reliable and valid measure of self-efficacy [93, 94] and is one of the most widely used measures of self-efficacy for coping with cancer [95].

##### Cardiopulmonary exercise testing (CPET)

At baseline, all participants will be screened for cardiac contraindications for exercise testing using a resting ECG to rule out unstable cardiac disease (e.g. acute myocardial infarction and unstable arrhythmia). The resting ECG will be reviewed immediately by a cardiac consultant or registrar who will provide the final say as to whether an individual is cleared to complete the CPET. Resting ECGs will be conducted at baseline, and CPET clearance will stand for the entirety of the trial. For individuals who are cleared to complete the CPET, the peak volume of oxygen (O_2_) consumed and used (VO_2peak_) will be assessed using an incremental ramped maximal exercise test on an upright Ergoselect bicycle ergometer (Ergoselect 100, Love Medical, Manchester, UK). Two researchers will be present during the testing. The test will begin with a 5-min baseline period, while the participant is sat upright on the cycle ergometer and resting respiratory values assessed (via breath-by-breath gas exchange monitoring and spirometry; Ergostik CPET system, Love Medical, UK). The participant will begin with a warm-up of unloaded cycling for 3 min. Following the warm-up, the resistance will increase continuously, V̇O_2_ peak will be assessed using an incremental ramped protocol of 10 to 25 W/min until volitional fatigue. Participants will be asked to maintain a constant cadence of 60–80 revolutions per minute (RPM). Participants will be provided with positive encouragement through the assessment and encouraged to ‘keep pushing’ towards the end of the assessment. The test will be terminated upon volitional exhaustion or when the cadence falls below 60 rpm. The increase in work rate was chosen to bring the participant to the limit of tolerance within 8 to 12 min. VO_2_peak will be defined as the highest 15-breath moving average for VO_2_ (in absolute [l/min] and relative [ml/kg/min] terms. Heart rate (12-lead ECG), oxygen saturation (ear pulse oximeter), blood pressure (automated brachial arm cuff) and rating of perceived exertion (Borg scale 6–20) will be assessed throughout CPET.

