### Eligibility

The eligibility criteria for the two pilot RCTs are outlined in Table 2.

**Table 2 Tab2:** Eligibility criteria for the two pilot RCTs

	**Inclusion criteria**	**Exclusion criteria**
CRANK-P	1. Men with D’Amico high-risk localised PCa (*PSA* > 20) or clinical stage ≥ cT2c or Gleason 8/9/10 [59] OR men with any N1 PCa OR men with metastatic PCa (stage M1) 2. Aged 18 years or over 3. Cleared for engaging in PA by the treating consultant	1. Engage in ≥ 150 min of MVPA per week as assessed by the Get Active Questionnaire [60] 2. Uncontrolled hypertension (systolic BP > 160 mmHg and/or diastolic BP > 90 mmHg), for which the individual is not taking medication 3. Comorbidities including myocardial infarction or stroke within the past 6 months or evidence of end-stage renal failure or liver disease, uncontrolled congestive heart failure or angina 4. Use of a mobility aid preventing cycling 5. No previous experience riding a bicycle 6. Any other contra-indications to exercise 7. Are unable to read and communicate in English
CRANK-B	1. Women or men with early BC (i.e. stages 1 or 2) who have completed their primary BC treatment (i.e. surgery, systemic therapy and/or radiation therapy) 2. Aged 18 years or over 3. Cleared for engaging in PA by the treating surgeon	1. Engage in ≥ 150 min of MVPA per week as assessed by the Get Active Questionnaire [60] 2. Individuals with metastatic disease 3. Uncontrolled hypertension (systolic BP > 160 mmHg and/or diastolic BP > 90 mmHg), for which the individual is not taking medication 4. Comorbidities including myocardial infarction or stroke within the past 6 months or evidence of end-stage renal failure or liver disease, uncontrolled congestive heart failure or angina 5. Use of a mobility aid preventing cycling 6. No previous experience riding a bicycle 7. Any other contra-indications to exercise 8. Are unable to read and communicate in English

*BC* breast cancer, *BP* blood pressure, *cT* clinical T category, *N* degree to which cancer has spread to lymph nodes, *M* degree to which cancer has spread to other areas of the body, *MVPA* moderate-to-vigorous physical activity, *NICE* National Institute of Health and Care Excellence, *PA* physical activity, *PCa* prostate cancer, *PSA* prostate-specific antigen

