#### Control group

Individuals assigned to the waitlist control after baseline data collection (T0) will receive two phone calls from the researcher at approximately weeks 4 and 8 to maintain engagement in the study. During these phone calls, the researcher will ask participants about how their cancer treatment is going and will direct participants to cancer support groups in line with standard care procedures. Between post-intervention data collection (T1) and 3-month follow-up data collection (T2), individuals will not be contacted. After the 3-month follow-up, individuals in the control condition will be offered training session 1 and loaned an e-bike for 3 months. Sessions 2, 3 and 4 will not be conducted. Participants will be asked to report any contact they have with other individuals in the study to ensure no contamination between conditions has occurred.

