#### Assessment of harm

Participants will be asked to report adverse events resulting from e-cycling (e.g. musculoskeletal problems, falls or road traffic incidents) by calling the study phone line. All adverse events will be immediately documented in the study master file and if required reported to the study sponsor and appropriate NHS trust as per standard procedures. Each month, the number and types of adverse events that have taken place will be shared with the Trial Steering Committee to determine whether it is appropriate for the trial to continue. Adverse events that mean the participant is unable to continue with the intervention will also be documented under retention rates. Qualitative interviews will be used to explore any unintended consequences that arise from participation in the study.

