#### Outcome measures

Unless stated otherwise, outcome measures will be assessed at baseline (T0), immediately post-intervention (T1) and at 3-month follow-up (T2) and will be collected in both trials.

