3. Can the intervention be implemented as intended?	• No. of training sessions attended by participants and additional contact with instructors • Extent to which intervention content is completed as planned • No. of and extent of adaptations	Intervention checklists		X			Frequencies and percentages
4. Are the intervention and study procedures acceptable to participants, instructors and clinical team?	• Acceptability of recruitment strategy to clinical team • Acceptability of intervention to participants • Acceptability of study procedures to participants • Acceptability of intervention delivery to instructors	Semi-structured interviews			X		Thematic analysis based on research question
5. What are participants experiences of e-cycling?	• Experiences of e-cycling • Participant’s barriers and facilitators to e-cycling	Semi-structured interviews			X		Thematic analysis based on research question
6. What is the potential effect of the intervention on a range of individual health and behavioural outcomes?	• Weight, BMI and waist circumference	Tanita digital scales, SECA 700, non-stretch take	X		X	X	Comparison of change scores between conditions Reporting of effect estimates with 95% CI
	• Metabolic markers (fasting glucose, insulin, insulin resistance, lipid profile, IGF-I, IGF-II, IGFBP-2, IGFBP-3, PSA^a^)	8-mL blood sample	X		X		
	• General health-related quality of life	EuroQol-5 dimension-5 level	X		X	X	
	• Cancer-specific quality of life	EORTC QLQ-C30 EORTC PR-25^a^ EORTC BR-45^b^	X		X	X	
	• Urinary health^a^	ICIQ-MLUTS	X		X	X	
	• Erectile dysfunction^a^	International Index of Erectile Function	X		X	X	
	• Fatigue	FACIT-F	X		X	X	
	• Self-efficacy for coping with cancer	Cancer Behaviour Inventory — Brief	X		X	X	
	• Cardiorespiratory fitness	Maximum oxygen uptake using cycle ergometer	X		X	X	
	• Hand grip strength	Hydraulic hand dynamometer	X		X	X	
	• Total physical activity (time spent in moderate-to-vigorous physical activity)	Axivity AX3	X		X	X	Comparison of change scores between conditions
	• Travel behaviour • No. of trips • Transport mode (walking, cycling, e-cycling, car, bus, train) • Trip purpose	QStarz GPS and travel diary	X		X	X	Mean and SD
	• E-cycling behaviour and intensity: no. of journeys, duration, distance travelled, purpose of use	Bike odometer, Fitbit Charge 5 GPS watch, logbook		X			Mean and SD

^a^CRANK-P only, ^b^CRANK-B only

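### Clearance for the maximal exercise test, based on one baseline resting ECG, is fixed by rule for the whole trial, although the test is repeated about 12 to 14 and 24 to 27 weeks later with no stated re-check

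*Protocol article*

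**What the plan says.** The CPET section of the protocol article has every participant screened at baseline with a resting ECG, "to rule out unstable cardiac disease (e.g. acute myocardial infarction and unstable arrhythmia"). A cardiac consultant or registrar reads it at once and decides whether the person may take the test. The section then fixes how long that decision lasts: "Resting ECGs will be conducted at baseline, and CPET clearance will stand for the entirety of the trial".

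The test is a maximal incremental ramp on a cycle ergometer. On stopping, the section says: "The test will be terminated upon volitional exhaustion or when the cadence falls below 60 rpm". Heart rate by 12-lead ECG, oxygen saturation, blood pressure and perceived exertion are recorded throughout, after a 5-minute seated period and 3 minutes of unloaded pedalling, with two researchers in the room.

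Under Outcome measures, the default schedule is that "outcome measures will be assessed at baseline (T0), immediately post-intervention (T1) and at 3-month follow-up (T2"). Table 3 agrees for fitness: the row labelled "Maximum oxygen uptake using cycle ergometer" is marked at T0, T1 and T2.

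**The concern.** The purpose of the ECG and the lifetime of the clearance do not fit together. Acute infarction and unstable arrhythmia, the protocol's own examples, are states of the heart at the time of the reading. A baseline trace can exclude them for the baseline test; it cannot do so for a test months later. The protocol treats a cardiac doctor's decision as necessary before the first maximal test, even though the same monitoring runs during that test. It then carries the decision forward to the second and third tests without condition.

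At stake is the safety of participants in both arms during the most strenuous procedure in the two trials. Because the text states the rule outright, this is not a detail that a condensed article has left to a fuller document: a fuller protocol that required re-clearance would contradict the sentence.

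**Working it through.** The protocol gives no figure for the age of the ECG, so there is none to reproduce. The age follows from the schedule.

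**Inputs**
- E-bike loan: 12 weeks (E-bike loan).
- Training before the loan: 0 to 2 weeks, because the second session falls within 2 weeks of the first and is held only if needed or wanted (E-bike training).
- T1 to T2: 3 months, taken as 12 to 13 weeks (Study design and setting).
- Number randomised: 40 per trial, 80 in all; anticipated retention about 80% (Sample size).

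**Age of the baseline ECG**
- At T1: 12 + 0 = 12 weeks, to 12 + 2 = 14 weeks.
- At T2: 12 + 12 = 24 weeks, to 14 + 13 = 27 weeks.

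Delays in booking training, the loan or the visits are ignored; any delay makes the reading older. For controls, T1 is assumed to fall at about 12 weeks, in line with the calls at about weeks 4 and 8.

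**Number of later tests covered by the rule**
- Full attendance, everyone cleared at T0: 80 × 2 = 160.
- 80% retention, assumed at both T1 and T2: 80 × 0.8 = 64, and 64 × 2 = 128.

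These counts are upper limits and describe the schedule, not risk. They serve only to size the work that a re-check would add.

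**What is stated at each test**

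| | T0 | T1 and T2 |
|---|---|---|
| Maximal ramp test | yes | yes |
| 12-lead ECG, blood pressure, saturation during the test | yes | yes |
| Resting ECG read by a cardiac doctor beforehand | yes | no, by rule |
| Re-check of new events or symptoms beforehand | not applicable | none stated |
| Stated stopping criteria | exhaustion, cadence | exhaustion, cadence |

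The later tests therefore have a current trace. They have no stated cardiac review of that trace, and no stated condition under which the baseline clearance lapses.

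**The case against.** The strongest reply is that the later tests are monitored by 12-lead ECG with two researchers present, and that staff who knew of a new infarction would hardly go ahead. Much of this stands. The rule does not oblige anyone to test a person known to be unwell, and an article may leave routine questioning at visits to the full protocol. Events may also come to light through the control calls and instructor sessions at weeks 4 and 8, or the weekly watch downloads for participants who do not pair the device.

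These routes are partial. None is described as cardiac screening. Under Assessment of harm, "Participants will be asked to report adverse events resulting from e-cycling", which does not cover an unrelated cardiac event. For controls, "Between post-intervention data collection (T1) and 3-month follow-up data collection (T2), individuals will not be contacted".

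Three stronger readings are tempting, and the document supports none of them.
- A reader might infer that 160 of 240 tests are done with no current cardiac reading. A trace is recorded at each one; only a stated doctor's review is absent, and the ratio merely says that two visits of three come after baseline.
- A reader might apply the Table 2 exclusion, "Comorbidities including myocardial infarction or stroke within the past 6 months", to the later tests. That criterion governs entry to the trial, not CPET clearance, and the ECG is not presented as a screen for stroke. Since T2 falls about 6 months after T0, almost any event in between would lie inside the window in any case.
- A reader might infer a special risk in CRANK-P, where 20 of 40 men are to be recruited soon after diagnosis and metastatic disease is allowed. That treatment falls between tests is an inference, and the document does not link treatment or stage to cardiac instability.

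**Conclusion.** The point holds as a modest safety improvement. A clearance whose stated purpose is to exclude an unstable condition is made permanent, and it then covers maximal tests about 12 to 14 and 24 to 27 weeks later with no stated re-check or cardiac doctor's review. The intervals rest on the stated durations with no scheduling delay and on 3 months being 12 to 13 weeks.

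No expected number of events can be given, because the protocol states no rate. Sample size, effect estimates and the primary feasibility outcomes are unaffected. The case for acting is that the fault lies in one sentence, the possible consequence is serious even if rare, and the remedy is cheap.

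**What to change.** Replace the sentence on the duration of clearance with:

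> Baseline ECG clearance carries forward to T1 and T2 only if the participant reports no new cardiac event, symptom, diagnosis or relevant treatment change since the last visit and the 12-lead trace in the rest period shows no evident new abnormality; otherwise the CPET is deferred until a cardiac consultant or registrar has reviewed the case.

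Add that anyone not cleared stays in the trial for all other measures.

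The cost is a few minutes at each of at most 160 later tests (128 at 80% retention) and occasional triggered reviews. No new equipment is needed, because the 12-lead ECG is already in place. Some VO2peak values at T1 or T2 will be missing; report these by arm with the reason.

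A cardiac doctor's reading before every later test is not proposed. It could mean up to 160 extra consultant or registrar readings, which is real clinical resource and out of proportion to the point.

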### Allocation, randomisation and blinding

Randomisation will occur after consent is obtained and baseline data (T0) has been collected. For each pilot RCT, 40 individuals will be randomly assigned to either the e-cycling intervention or waitlist control in a 1:1 allocation ratio. For CRANK-P, individuals will be stratified based on cancer treatment received prior to randomisation. For CRANK-B, individuals will be stratified based on stage of cancer treatment prior to randomisation. Permuted blocks of random size will be used. A random allocation sequence will be generated by an independent statistician using R v4.1.2, package blockrand (v1.5). The randomisation sequence will be accessible through a password-protected Excel file. The researcher will access the Excel file and allocate the participant to either condition in the order issued in the sequence. Researchers will be aware of the group allocation. Participants will be informed of the group allocation via telephone by a member of the research team. Blinding of intervention allocation will not be possible for any participant involved in the trial or the researchers.

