##### Hand-grip strength

Participant’s hand-grip strength will be measured on each hand using a hydraulic hand dynamometer (Jamar Hand Dynamometer, USA) which can measure isometric grip force up to 90 kg. This device has been found to have good reliability and reproducibility [96]. The device will be calibrated at the start of each measurement day. Each participant will be asked to sit upright on a chair with their forearm on the armrest and then grasp the handle of the device in their right hand. Participants are required to maintain a 90° angle in their elbow adjacent to their side so that their thumb faces upwards while squeezing the handle as strongly as possible for approximately 3 s. The same protocol will be applied to the left hand. The measure will be repeated three times on each hand. Standardised encouragement will be provided during the assessment. The average values of the two hands will be used.

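### VO2peak comes from a volitional test coached by researchers who know the allocation, and the effort data recorded in the test have no stated role in its interpretation

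*Protocol article*

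**What the plan says.** The relevant text is in three places in the Protocol article.

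- **Allocation, randomisation and blinding:** "Researchers will be aware of the group allocation", and "Blinding of intervention allocation will not be possible for any participant involved in the trial or the researchers". No separate masked assessor is named. Randomisation follows baseline measurement, so the T0 test is done before allocation is known and the T1 and T2 tests after it.
- **Cardiopulmonary exercise testing (CPET):** "Two researchers will be present during the testing". The ramp is 10 to 25 W/min, chosen so that the participant reaches the limit in 8 to 12 min. On stopping: "The test will be terminated upon volitional exhaustion or when the cadence falls below 60 rpm". On coaching: "Participants will be provided with positive encouragement through the assessment and encouraged to ‘keep pushing’ towards the end of the assessment". Heart rate is followed by 12-lead ECG, and "rating of perceived exertion (Borg scale 6–20) will be assessed throughout CPET". Gas exchange is described as breath by breath for the resting period, and the 15-breath definition of VO2peak implies that this continues during exercise. VO2peak is the highest 15-breath moving average, with no condition attached.
- **Hand-grip strength:** "Standardised encouragement will be provided during the assessment".

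Table 3 lists cardiorespiratory fitness under research question 6 (potential effect), measured at T0, T1 and T2. It labels the measure as maximum oxygen uptake and plans a comparison of change scores with 95% confidence intervals. The Discussion mentions lack of blinding only as a threat to retention.

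**The concern.** A peak value from a test that the participant ends depends on how hard the participant is willing to push and on how hard staff urge them on. Encouragement is stepped up in the closing phase, which is where the peak is set, and at T1 and T2 the people giving it know the arm. The participants know it too. By T1 one arm has had an e-bike for 12 weeks, while the other is still waiting for its loan. Motivation and ease on a cycle ergometer may therefore differ by arm without any difference in fitness. Subtracting the T0 value does not remove this, because T0 precedes allocation.

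The pilot is meant to judge promise, supply a standard deviation for a later sample size and help choose outcomes for a definitive trial. Uneven effort can distort all three. The planned confidence interval reflects sampling error only and would not reveal the problem. Data that would help to reveal it are collected, but the article gives them no role.

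**Working it through.** The article gives no standard deviation, expected effect or threshold of promise for VO2peak, so there is no planned figure to reproduce. The check is to set the passages side by side and then bound the size.

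**Text check**

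| Feature | CPET | Hand-grip |
|---|---|---|
| Encouragement given | yes, stepped up at the end | yes |
| Called standardised | no | yes |
| Tester masked to arm | no | no |
| Effort indicators recorded | heart rate, Borg RPE, gas exchange | none stated |
| Stated use of those indicators in the outcome | none | not applicable |

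**Size**

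Inputs from the article: ramp 10 to 25 W/min and time to limit 8 to 12 min, taken here as the ramp phase after the warm-up. Assumptions: body mass 80 kg, VO2peak 20 mL/kg/min (80 × 20 = 1,600 mL/min), 10.3 mL O2 per W, and a mean difference between arms of 30 s in stopping time.

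*Formula.* With ramp duration D, oxygen cost k per W and oxygen uptake V0 at the start of the ramp, the ramp rate is r = (VO2peak − V0)/(k·D). Riding on for a further time t adds k·r·t = (VO2peak − V0)·t/D. The constant k cancels.

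*Upper bound, V0 = 0 (all uptake credited to the ramp), t = 0.5 min:*
- D = 8 min: 1,600 × 0.5/8 = 100 mL/min. 100/80 = 1.25 mL/kg/min, or 6.25%.
- D = 12 min: 1,600 × 0.5/12 = 66.7 mL/min. 66.7/80 = 0.83 mL/kg/min, or 4.2%.

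*Allowing an assumed V0 of 400 to 600 mL/min for unloaded cycling:*
- D = 8 min: 1,200 × 0.0625 = 75 mL/min (0.94 mL/kg/min, 4.7%), down to 1,000 × 0.0625 = 62.5 mL/min (0.78 mL/kg/min, 3.9%).
- D = 12 min: 1,200 × 0.0417 = 50 mL/min (0.63 mL/kg/min, 3.1%), down to 1,000 × 0.0417 = 41.7 mL/min (0.52 mL/kg/min, 2.6%).

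If VO2 flattens near the limit, the true values are lower.

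**What the confidence interval can show.** With 20 per arm and the anticipated 80% retention, 20 × 0.8 = 16 per arm. The half-width for a difference in mean change is 1.96 × √(2/16) = 0.69 SD of the change score. That describes random error around whatever the test measures. A systematic difference in effort moves the estimate and leaves the interval's width unaffected.

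**The case against.** The strongest reply has four parts.

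1. *Effort data are taken.* A reader might infer that the test has no effort check at all. The article does not support that: heart rate and Borg RPE are recorded throughout, and breath-by-breath gas exchange allows RER and a ventilatory threshold to be derived. The gap is in stated use, not in collection.
2. *Procedure detail belongs elsewhere.* A fuller protocol or test procedure may hold an encouragement script and a rule for carrying the ramp rate over to later visits. This largely stands. The article is silent on a script, which does not show that the encouragement is unscripted, and the missing script or ramp rule would not be a point alone. What remains is the combination that the article does fix: a volitional end point, testers who know the arm, encouragement in the deciding phase, and a peak value taken without reference to the effort data. The contrast with the hand-grip wording is in the article's own text.
3. *The size is easily overstated.* Someone might take 25 W/min for the participant assumed above: 12.5 W in 30 s, × 10.3 = 129 mL/min, /80 = 1.61 mL/kg/min, or 8% of 20. The protocol's timing rule excludes that pairing. 1,600/10.3 = 155 W at most, reached in 155/25 = 6.2 min, short of the 8 min minimum. Someone who lasts 8 min at 25 W/min reaches 200 W, so VO2peak is at least 200 × 10.3/80 = 25.75 mL/kg/min, and 1.61 is then at most 6.25% of it. Nor does the article give a source for 30 s, which must hold as a mean difference between arms.
4. *The outcome is secondary.* The primary outcomes concern feasibility, no p-values are planned, and VO2peak is one of many measures. The article does not rank it as the main objective outcome. This stands and limits the weight of the point, but an estimate with an interval can still be biased.

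It is also tempting to say that the bias must favour the intervention. That is likely at T1, but not shown. It is weaker at T2, because loan bikes are returned at week 12 and later access is optional.

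**Conclusion.** The point holds in a limited form. As written, the plan allows a difference in effort between arms at T1 or T2 to appear as a difference in cardiorespiratory fitness, and it assigns no use to the recorded data that could show this. For a mean 30 s difference in stopping time, the distortion is at most about 4% to 6% of VO2peak (0.8 to 1.25 mL/kg/min). With a realistic allowance for unloaded cycling it is about 2.6% to 4.7% (0.5 to 0.9 mL/kg/min). These figures rest on the assumed 80 kg, 20 mL/kg/min, 400 to 600 mL/min unloaded uptake and 30 s, and on the protocol's 8 to 12 min ramp. They are illustrative: the article gives no basis for saying how large an effort difference will be, or whether a shift of this size would be taken as promise. The consequence is confined to a secondary outcome of a pilot, but the remedy costs little and is worth adopting.

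**What to change.** Keep the test and the staff, and add three things to the CPET and analysis text.

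1. State that CPET encouragement is standardised, as for hand-grip, and that each participant's T0 ramp rate is reused at T1 and T2.
2. Report peak RER, peak heart rate and peak RPE by arm and visit beside VO2peak. Do not restrict the comparison to tests that pass an effort criterion: effort is measured after randomisation and may differ by arm, so that subset would lose the protection of randomisation, with only about 16 per arm to start from.
3. Derive VO2 at the ventilatory threshold from the existing breath-by-breath files, read under participant ID without knowledge of arm or visit, and report it beside VO2peak as a less effort-dependent measure.

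The cost is protocol wording and some extra processing of files already held. A few tests may have no identifiable threshold. A participant whose fitness changes may fall outside the 8 to 12 min target on the retained ramp, and such tests should simply be noted.
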